## Abstract

One of the most important components of sepsis management is hemodynamic restoration. If the target mean arterial pressure (MAP) is not obtained, the first recommendation is for volume expansion, and the second is for norepinephrine (NE). We describe the methodology of a randomized multicenter trial aiming to assess the hypothesis that low-dose NE given early in adult patients with sepsis will provide better control of shock within 6 hours from therapy starting compared to standard care. This trial includes ICU septic patients in whom MAP decrease below 65 mmHg to be randomized into 2 groups: early NE-group versus standard care-group. The patient’s attending clinician will determine how much volume expansion is necessary to meet the target of a MAP > 65 mm Hg. If this target not achieved, after at least 30 ml/kg and guided by the available indices of fluid responsiveness, NE will be used in a usual way. The latter must follow a consensual schedule elaborated by the investigating centers. Parameters to be taken at inclusion and at H6 are: lactates, cardiac ultrasound parameters (stroke volume (SV), cardiac output (CO), E/E’ ratio), and P/F ratio. MAP and diuresis are recorded hourly. Our primary outcome is the shock control defined as a composite criterion (MAP > 65 mm Hg for 2 consecutive measurements and urinary output > 0.5 ml/kg/h for 2 consecutive hours) within 6 hours. Secondary outcomes: Decrease in serum lactate> 10% from baseline within 6 hours, the received fluid volume within 6 hours, variation of CO and E/E’, and 28 days-Mortality. The study is ongoing and aims to include at least 100 patients per arm. This study is likely to contribute to support the indication of early initiation of NE with the aim to restrict fluid intake in septic patients. **(ClinicalTrials.gov ID: NCT05836272).**

## Introduction

Sepsis is characterized by a systemic inflammation triggered with a severe infection and leading to inappropriate host response against infection. Typically, a vasoplegia with capillary leakage is noteworthy at the microcirculatory level [1]. The etiologic component of sepsis management involves the use of antibiotics and source elimination; symptomatic therapies include hemodynamic restoration and support for failing organs [2].

It is commonly recognized that hemodynamic restitution starts with volume expansion, when patient is thought to be afluid responder. Vasopressors, mainly norepinephrine (NE) as first-line therapy, should be used when mean arterial pressure (MAP) remains below the target after optimization of intravascular volume [2].

NE should be given as soon as sepsis resuscitation begins, according to a number of recent studies [3–5]. Indeed, when NE was administrated earlier than usually recommended, it improved MAP and cardiac output with a favorable effect on mortality [6]. At a median interval of 1.3 hours from ICU admission and exclusive administration of NE, MAP was adequately restored within a relatively short time (30 min) [7].

Furthermore, in comparable patients, it was linked to a greater survival than that predicted by severity scores [7]. In the same way, a retrospective study showed that the time to initiate NE was an independent factor of mortality [4]. In the subgroup that received early NE, the duration of hypotension and NE administration were shorter and the total dose of NE was lower than in the subgroup that received late NE [4]. On the other hand, giving lot fluids increases the risk of fluid overload, which worsens the prognosis for septic patients [8]. In the recent “CENSER” trial [5], the shock was controlled in 76%of patients in the early NE group versus 48% (p<0.001). In addition, the authors demonstrated that the incidences of cardiogenic pulmonary edema and recent arrhythmia were lower in the early NE group with respectively 22/155 (14.4%) vs 43/155 (27.7%), p = 0.004 and 17/155 (11%) vs 31/155 (20%), p = 0.03. In light of these arguments, it is tempting to limit fluid prescription at the early phase of hemodynamic control in septic states; by initiating NE early.

### Aim

We aim to assess the hypothesis that low-dose of NE given early, as soon as hypotension due to sepsis occur, and will provide better control of shock within 6 hours of treatment. This therapeutic regimen will be compared to standard care (including expansion with crystalloids, appropriate antibiotics, eradication of infection source and support of associated organ failure). Secondly, we seek to determine the effect of early NE on the administered fluid volume, cardiac output and the lactate level.

## Materials and methods

### Trial design

This is a multicenter parallel-group, randomized, interventional, active controlled trial. The 1:1 allocation ratio is regularly checked.

### Participants, eligibility criteria, and settings

The study is conducted in 11 Tunisian medical ICUs: Rabta, Ariana, severe burns department, Zaghouan, Habib Thameur Center, Mahdia, Farhat Hached Sousse Center, Sfax, Bizerte, Tunis Urgent Medical Assistance Center, and Mahres. The recruitment period for this study is scheduled to begin on September 15, 2023 and end over one year, i.e. September 15, 2024. Are eligible for our trial, all patients aging 18 or older, admitted in ICU, who present sepsis and a decrease in MAP below 65 mmHg. According to the sepsis 3 definitions update [1], sepsis is defined as an organ dysfunction caused by a documented or suspected infection. Organ dysfunction is represented by an increase in the Sequential [sepsis-related] Organ Failure Assessment (SOFA) score of 2 points or more. Exclusion criteria are: pregnancy, surgery indication, neoplasia, circumstances where fluid restriction is the rule (acute cardiogenic pulmonary edema…).

It should be noted that sepsis is only considered for inclusion when it occurred in the ICU to minimize the interventional bias. Septic patients who started receiving fluid therapy or vasopressive agents in their original departments (emergency or others) are excluded. Patients who die before primary outcome assessment are considered treatment failure.

In accordance with ethical principles of international guidelines including the Declaration of Helsinki, Council for International Organizations of Medical Sciences (CIOMS) International Ethical Guidelines, and International Conference on Harmonization (ICH) Good Clinical Practice (GCP) Guidelines, the protocol and other relevant documents are reviewed and approved by the institutional ethics Committee of the Northern Data Protection Committee of Tunisia on 11/04/2023 (CPP_37_2022_SI_noradrénaline) (supplement document). A written and informed consent is obtained from all patients or their legal representative. In case of urgent inclusion, we opt to call the legal parents to find out who can provide oral consent—or not; after explaining the study and its objectives. If oral consent is provided, the written consent will be completed the next day.

### Interventions

As soon as hypotension secondary to sepsis occur, the early NE arm receives the low-dose NE in addition to the standard therapeutic regimen that complies with the 2021 Surviving Sepsis Compaign (SSC) guidelines [2]. The low-dose NE is defined as a posology not strictly exceeding 0.25 mg per hour. The NE (Norepinephrine Bitartrate) is prepared as follows: 4 mg mixed with 250 ml of 5% glucose resulting in a final norepinephrine concentration of 0.016 mg/ml. For the placebo group, 250 ml of 5% glucose will be prepared. Both drugs will be infused via a peripheral line or a venous catheter. The intravenous infusion rate varies from 8 to 15 ml/hour, which is to be adjusted according to the body weight to obtain norepinephrine at 0.05 microgram/kg/min (ie 0.128 to 0.24 mg per hour) in continuous infusion. The placebo arm receives only the classic therapeutic regimen that complies with the 2021 SSC guidelines.

Standard Treatment regimen for sepsis includes expansion with crystalloid solution, appropriate antibiotics, control of the infection source, and support of associated organ failure (invasive ventilation, purification extra-renal…). The flow rate and volume of fluid expansion will be under the judgment of the clinician in charge and having for a hemodynamic objective a MAP > 65 mm Hg, in normotensive patients, and a higher threshold at 70–75 mm Hg in hypertensive patients. If this objective is not reached, after an optimal filling (at least 30 ml/kg), NE is authorized according to a usual schedule. Volume expansion is guided by the available indices of fluid responsiveness such passive leg raising (PLR), central venous pressure (CVP) variation, pulse pressure variation (PPV), ultrasound Inferior vena cava: (US-IVC) variation, etc…The common protocol for prescribing NE according to the usual schedule is as follows: norepinephrine by continuous intravenous injection, pure, and by electric syringe pump. The initial dosage is 1 mg/hour, the equivalent of 1 ml/hour. Then titrate according to the MAP to reach 65 mm Hg.

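### The weight-based norepinephrine dose fits the stated rate range only from 42.7 to 80 kg, and above 83.3 kg it exceeds the limit that defines low-dose treatment

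*Protocol article*

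**What the plan says.** The Interventions section of the protocol article fixes the early NE regimen with four linked statements.

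- Definition of low dose: "The low-dose NE is defined as a posology not strictly exceeding 0.25 mg per hour". I read this as a maximum of 0.25 mg/hour.
- Preparation: "4 mg mixed with 250 ml of 5% glucose resulting in a final norepinephrine concentration of 0.016 mg/ml".
- Rate: "The intravenous infusion rate varies from 8 to 15 ml/hour, which is to be adjusted according to the body weight".
- Target of that adjustment: "to obtain norepinephrine at 0.05 microgram/kg/min (ie 0.128 to 0.24 mg per hour) in continuous infusion".

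The section on participants and eligibility admits "all patients aging 18 or older, admitted in ICU, who present sepsis and a decrease in MAP below 65 mmHg". The exclusions begin "Exclusion criteria are: pregnancy, surgery indication, neoplasia, circumstances where fluid restriction is the rule", and the same section also excludes patients who were already given fluids or vasopressors elsewhere. Neither list mentions body weight.

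**The concern.** A dose fixed per kilogram has no upper or lower bound in mg/hour unless body weight is bounded. The article nevertheless treats a fixed per-kilogram dose as the same thing as a fixed mg/hour range, and places an absolute hourly limit on top. These can hold together only over a limited span of weights, while eligibility leaves weight open.

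What is at stake is the definition of the tested intervention. Eleven ICUs apply the regimen. For a heavy patient, one centre can follow the per-kilogram figure and another the rate range or the limit, each with support in the text. The dose then depends on the centre's reading as well as on weight, and the trial report could not state accurately that the early NE arm received 0.05 microgram/kg/min.

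**Working it through.** **Inputs** (all from Interventions): 4 mg in 250 ml; rate 8 to 15 ml/hour; target 0.05 microgram/kg/min; limit 0.25 mg/hour.

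**Step 1: reproduce the article's own figures.**
- Concentration: 4 / 250 = 0.016 mg/ml, as stated.
- Lower dose: 8 × 0.016 = 0.128 mg/hour, as stated.
- Upper dose: 15 × 0.016 = 0.24 mg/hour, as stated.

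**Step 2: express the target per hour.** 0.05 microgram/kg/min × 60 / 1000 = 0.003 mg/kg/hour. The rate needed is 0.003 / 0.016 = 0.1875 ml/hour per kg.

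**Step 3: weights at which the statements meet.**
- 8 ml/hour: 0.128 / 0.003 = 42.7 kg.
- 15 ml/hour: 0.24 / 0.003 = 80.0 kg.
- 0.25 mg/hour limit: 0.25 / 0.003 = 83.3 kg, which corresponds to 0.25 / 0.016 = 15.6 ml/hour.

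**Step 4: individual weights.** The weights are chosen for illustration. The last column is the dose received if the rate is kept within 8 to 15 ml/hour, that is, rate × 0.016 × 1000 / (60 × kg).

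| Weight (kg) | mg/hour needed for 0.05 | ml/hour needed | Conflicts with | microgram/kg/min if rate kept at 8–15 |
|---|---|---|---|---|
| 40 | 0.120 | 7.5 | rate minimum | 0.053 |
| 60 | 0.180 | 11.25 | nothing | 0.050 |
| 80 | 0.240 | 15.0 | nothing | 0.050 |
| 85 | 0.255 | 15.9 | rate maximum and limit | 0.047 |
| 90 | 0.270 | 16.9 | rate maximum and limit | 0.044 |
| 100 | 0.300 | 18.75 | rate maximum and limit | 0.040 |
| 120 | 0.360 | 22.5 | rate maximum and limit | 0.033 |

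**Step 5: size of the gap.**
- At 100 kg, 0.040 / 0.05 = 0.80, so 20% below the stated dose. Two centres following different statements would run 15 and 18.75 ml/hour; 18.75 / 15 = 1.25, a 25% difference.
- At 120 kg, 0.033 / 0.05 = 0.67, so about 33% below.
- If the 0.25 mg/hour limit is used instead of 15 ml/hour, the 100 kg patient receives 0.25 × 1000 / (60 × 100) = 0.042 microgram/kg/min, still about 17% below.
- At 40 kg, 0.128 / 0.120 = 1.067, so about 7% above, or 0.008 mg/hour.

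**The case against.** The best defence is that the regimen is a weight-based dose inside a range with a ceiling: the rate rises with weight and stops at the top. The mg/hour range in parentheses supports this, since the authors bound the per-kilogram dose themselves. The reading is plausible, but the text does not state it. It says the rate is adjusted in order to reach the per-kilogram target, and if a ceiling is meant, that target is not the dose given to heavier patients.

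A second defence is that "The intravenous infusion rate varies from 8 to 15 ml/hour" merely describes usual rates. That would dispose of the conflict between 80 and 83.3 kg and of the one below 42.7 kg. It leaves the conflict above 83.3 kg, because the 0.25 mg/hour figure is the trial's own definition of low dose.

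A third is that a journal article leaves detail to the full protocol. That would answer a complaint about a missing rate table. It does not answer this point, because the article prints all the figures and equates two of them.

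Several stronger conclusions might be inferred, and the documents do not support them:
- *The arithmetic is wrong.* It is not; every printed conversion reproduces.
- *Both weight extremes break the hourly limit.* Only the upper end does. At low weight the 0.25 mg/hour limit plays no part.
- *Adherence cannot be judged.* A delivered rate can be checked against the rate range and the limit in every patient. Only adherence to the per-kilogram figure outside 42.7 to 80 kg is ambiguous.
- *Many patients are affected.* No weight distribution is given, so the share cannot be calculated.
- *The primary comparison is biased.* Weight precedes randomisation and the analysis is by intention to treat. The ambiguity blurs what was tested; nothing here shows that it favours an arm.

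**Conclusion.** The point stands as a conflict between stated rules at weights that eligibility allows. All the figures agree from 42.7 to 80 kg. Between 80 and 83.3 kg only the rate maximum is exceeded, by at most about 0.6 ml/hour (15.6 − 15). Above 83.3 kg the per-kilogram dose and the limit that defines the intervention cannot both hold, and this is the substantive part. Below 42.7 kg only the rate minimum conflicts, with little consequence near that boundary.

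The shortfall, if the rate maximum is kept, is 20% at 100 kg and about 33% at 120 kg. These are illustrations for single patients, not an estimate for the trial. The result rests on reading the definition of low dose as a maximum of 0.25 mg/hour and on the absence of any weight criterion in the eligibility section. It does not depend on alpha, power or sample size.

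**What to change.** The responsible clinicians should reconcile three statements in Interventions (the weight-based dose, the rate range and the hourly limit) with each other and with the eligibility criteria, and state which one governs where they diverge. The outcome should be one rule that every centre applies at every eligible weight. This review does not say which figure that should be.

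The trial report should then describe the early NE dose as delivered, in microgram/kg/min, rather than assume 0.05 throughout. Most of what this needs is already planned: the Discussion foresees quantifying the cumulative NE dose, and weight is required for the 30 ml/kg filling threshold and for urine output in ml/kg/h. If the cumulative total pools the study infusion with NE given on the usual schedule, the study infusion should be kept separable.

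The cost is one clarification of the text and a notice to the centres. Sample size, randomisation and the primary analysis do not change. Because the article describes the study as ongoing, the clarification applies from its date, and patients already treated should be reported at the dose they received.

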### Studied variables

Multiple and repeated measures are incorporated in the study design to ensure data integrity.

**At baseline:** clinical data related to the patient and septic state, hemodynamic status (in particular MAP, diuresis), biological data (blood gases with lactate), echocardiography parameters (stroke volume (SV), cardiac output (CO) and E/E’ ratio), hourly monitoring of MAP and urine output for 6 hours, hemodynamic objective achieved or not? and when? **At H6:** blood gases (P/F ratio and lactates) plus echocardiography parameters, quantity of fluids received over 6 hours. **Evolutionary parameters:** mortality, ventilation, hemodialysis, length of stay, etc.Note that all details of the EA-NE-S-TUN schedule of the study protocol are displayed in **Fig 1**.

**Fig 1 pone.0307407.g001:**
[figure not shown]
Spirit schedule of the study protocol. Once sepsis with hypotension is diagnosed in and consent is obtained, he is eligible and according to randomization he is allocated either to the early NE or placebo group. Are recorded clinical and biological data (blood gases, lactate, ionogram and renal function), basic cardiac echocardiography (stroke volume (SV), cardiac output (CO) and E/E’ ratio in addition to standard care according to SSC 2021, measurement of MAP every 15 mn and hourly monitoring of urine flow until H6. At H6: in addition to the clinical parameters of interest (MAP and diuresis), lactate levels, echo cardiographic parameters and fluid received. Clinical monitoring will be carried out until discharge in order to determine Vasopressors free days, ICU stay, ventilator free days, and 28 days-Mortality.

### Outcomes (primary and secondary)

Our Primary Outcome is the shock control defined by a composite criterion (MAP > 65 mm Hg for 2 consecutive measurements AND urinary output > 0.5 ml/kg/h for 2 consecutive hours) within 6 hours. Secondary Outcomes are: Variation of CO (the 15% threshold is considered to define an increase in CO) within 6 hours, decrease in serum lactate > 10% from baseline within 6 hours, Quantity of intravenous fluid received, Improvement of SOFA at H24, vasopressors free days, ICU stay, ventilator free days, and 28 days-Mortality.

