### Statistical analyses planned

Enrollment of at least 96 participants per group would provide a statistical power at 90% to assess the difference in the primary outcome between the two groups at a two-sided alpha error of 0.05. All primary and secondary outcomes analyses are based on the intention-to-treat principle. The primary outcome and other categorical variables are evaluated by the chi-square test or Fisher exact test, where appropriate. The independent link between early NE and shock resolution will be evaluated using proportion regression (Beta regression approach). Under violations of normality/Gaussian assumptions, we will employ the Wilcoxon-Mann-Whitney test to assess group differences for continuous variables. For the 28-day mortality analysis, time to death is calculated from date of sepsis diagnosis to date of death. Survival distributions in the two groups are estimated by Kaplan-Meier curves. Values of p less than 0.05 are considered to indicate statistical significance. All data analyses will be performed using SPSS Statistics version 20 (SPSS Inc.). Missing data will be handled using the imputation approach.

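### Lactate is defined only as a fall of more than 10%, the status of the 15% cardiac output threshold is unclear, and the tests named for both do not adjust for baseline

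*Protocol article*

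**What the plan says.** The Outcomes section lists, among the secondary outcomes, "Variation of CO (the 15% threshold is considered to define an increase in CO) within 6 hours, decrease in serum lactate > 10" per cent from baseline, also within 6 hours. The Abstract gives the same lactate definition. No continuous lactate outcome is listed. The Abstract mentions CO with no threshold and adds the filling-pressure ratio: "the received fluid volume within 6 hours, variation of CO and E/E"'.

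The Aim is worded in terms of levels. It seeks to "determine the effect of early NE on the administered fluid volume, cardiac output and the lactate level".

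Both measures are taken twice: "Parameters to be taken at inclusion and at H6 are: lactates, cardiac ultrasound parameters". The Studied variables section confirms this.

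Under Statistical analyses planned, categorical variables go to a chi-square or Fisher test. Where normality fails, "we will employ the Wilcoxon-Mann-Whitney test to assess group differences for continuous variables". The only regression model named is a beta regression for shock resolution. None is named for lactate or CO.

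Eligibility covers adults in intensive care "who present sepsis and a decrease in MAP below 65 mmHg". No minimum lactate is required.

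**The concern.** The article collects a continuous measure before and after treatment, asks about the effect on its level, and for lactate then reports only which side of a percentage cut-off each patient falls. Patients whose lactate falls by 11% and by 60% count the same; patients at 9% and 11% count as opposites.

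The cut-off also fits this population poorly. Patients with normal lactate can enter, and for them a fall of clinically negligible size passes a 10% threshold.

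For CO, two readers of the Outcomes section could run two different analyses: a comparison of continuous changes, or a comparison of the proportions rising by more than 15%. The Discussion presents the immediate effect on stroke volume and CO as one of two limitations of the cited earlier trial that this trial sets out to overcome. An open choice between analyses, or a weak one, therefore undercuts one of the trial's claimed advances. What is at stake is the precision and clarity of secondary results.

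**Working it through.** The article gives no effect size, SD, response rate or correlation for lactate or CO, so there is no planned figure to reproduce for these outcomes. The 96 per arm in Power and sample size belongs to the primary outcome and is used here only as the number of patients.

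**1. Loss from the cut-off alone.** On the log scale a fall of more than 10% is a log-ratio below log 0.9, so the percentage rule is a cut-off on a change. If that change is roughly normal (assumed) and a proportion q respond, the efficiency of the responder comparison relative to the continuous one is φ(z_q)² / [q(1−q)].

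| Response rate | Efficiency | Information lost |
|---|---|---|
| 50/50 | 0.637 | 36% |
| 60/40 | 0.622 | 38% |
| 70/30 | 0.576 | 42% |
| 80/20 | 0.490 | 51% |

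**2. Loss from leaving baseline out as a covariate.** With equal SD at both times and baseline–H6 correlation ρ (both assumed), the change score has variance proportional to 2(1−ρ) and ANCOVA to 1−ρ². The ratio is (1−ρ²)/[2(1−ρ)] = (1+ρ)/2:

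- ρ = 0.4: 0.70
- ρ = 0.5: 0.75
- ρ = 0.6: 0.80
- ρ = 0.8: 0.90

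**3. Both together, at a median split.**

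- ρ = 0.4: 0.637 × 0.70 = 0.446, a loss of about 55%
- ρ = 0.8: 0.637 × 0.90 = 0.573, a loss of about 43%

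With 96 per arm this corresponds to 0.446 × 96 ≈ 43 to 0.573 × 96 ≈ 55 patients per arm analysed by ANCOVA.

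**4. The same in power.** At 96 per arm, an effect detectable with 80% power on the continuous change is (1.960 + 0.842) × √(2/96) = 0.404 SD.

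- Cut at the control median, the response rates are 50% and 65.7%, and power is 60%.
- At control response rates of 60%, 70% and 80%, power is 57%, 52% and 44%.
- The continuous analysis with baseline as covariate has power of 94%, 90% and 86% for ρ = 0.3, 0.5 and 0.7.

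**5. Normal lactate.** From a baseline of 1.0 mmol/L, 10% is 0.1 mmol/L, so any fall just above 0.1 is a response. Suppose nothing truly changes and each measurement has a fixed error SD s. The chance of an apparent response is Φ(−0.1 × baseline / (s√2)).

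| Baseline (mmol/L) | s = 0.1 | s = 0.2 | s = 0.3 |
|---|---|---|---|
| 1.0 | 24% | 36% | 41% |
| 2.0 | 8% | 24% | 32% |
| 4.0 | 0.2% | 8% | 17% |
| 6.0 | <0.1% | 2% | 8% |

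These error SDs are assumptions; the article gives none. The pattern, with false responses concentrated at low baseline, depends on error being roughly constant in absolute terms.

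**6. CO, if the 15% threshold is the outcome.** With a per-measurement CV of 5%, 10% or 15% (assumed) and no true change, 2%, 16% or 25% of patients would show a rise above 15%.

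**The case against.** The strongest reply is that a randomised comparison of responders or of changes is valid without covariate adjustment, that covariates for secondary outcomes are usually settled in the analysis plan, and that only a condensed article is shown. This stands in part. The missing covariate alone would be a weak point. The lactate definition is different: the article states it, as a cut-off, in two places, and an analysis plan would not ordinarily redefine a published outcome.

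A reader might infer more than the text supports:

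- **That CO is reduced to a cut-off.** The Outcomes wording can be read as a continuous variation with 15% as a label. The Abstract gives no threshold, and a test for continuous variables is planned. The fault for CO is ambiguity, and the loss in step 1 arises only under one reading.
- **That the baseline value is thrown away.** It is used to form both the lactate fall and the CO variation. What is absent is its use as a covariate.
- **That stroke volume and the P/F ratio suffer in the same way.** They are measured, but they are not listed outcomes and carry no threshold.
- **That noise creates a false treatment effect.** Error that is equal in the two arms mainly dilutes the contrast. The Discussion already acknowledges echocardiography variability and recommends a senior's presence.

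**Conclusion.** The point holds for lactate as a stated choice and for CO as an ambiguity. The lactate outcome loses about 36% of the information at a 50% response rate and about 51% at 80/20. Adding the missing baseline covariate brings the loss at a median split to about 43–55% for correlations of 0.8 down to 0.4. It is tempting to say flatly that half the information is discarded, but the documents do not support that. The figure depends on an assumed correlation, a roughly normal change on the log scale, equal spread at both times and an assumed response rate. For CO the combined loss applies only if the 15% threshold is the outcome; read as a continuous change, CO loses only the 10–30% in step 2.

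That a trivial fall from a normal lactate counts as a response follows from the eligibility and outcome wording alone. All of this concerns secondary outcomes; the primary outcome and its analysis are unaffected.

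**What to change.** State that CO variation is analysed as continuous. Make the main analysis of these secondary outcomes an ANCOVA of H6 log-lactate, H6 CO and H6 E/E' (listed in the Abstract), with treatment, the outcome's own baseline value, and the age and SOFA randomisation strata as covariates. Report the adjusted difference with its 95% CI, and use a rank-based version if the residuals are clearly non-normal. Keep the proportions with a lactate fall above 10% and a CO rise above 15% as supplementary descriptions.

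No new measurement is needed, since both time points are already recorded. The small cost is a rule for patients with no H6 value, through early death or because lactate is not available around the clock in some centres, as the Discussion notes. The general statement that missing data will be imputed does not settle how a death before H6 enters these outcomes, and the responder analysis needs the same rule. The change should be written down before the data are analysed, so that the choice cannot appear to follow the results.

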## Discussion

In this multicenter RCT, we plan to include at least 200 patients (n = 100 per group), which is, to our knowledge, the first and largest RCT involving almost all Tunisian ICUs reported to date. During the preparation of this manuscript, the methodology diffusion via several meetings between the investigators is taking place. We plan to close the study inclusion in September 2024.

The trial’s methodology requires a certain level of attention; particularly during the first six hours. Indeed, during this time interval, the patient is enrolled in his trial group, basic data (hemodynamic parameters, echocardiography and lactate level) are collected, quantity of volume expansion is determined (while being guided by responsiveness indices and monitored by hourly intakes of MAP, diuresis, heart rate, skin recoloration time, etc…), labeling a success or failure status according to the defined endpoint composite criterion. This entire assessment will be redone at H6 in order to assess the effect of the tested action (early NE or standard care) on the stroke volume, cardiac output, LV filling pressures and on the drop in lactate. The received fluids volume over the 6 hours and the total cumulative dose of NE administered during the septic episode will be also quantified.

Concerning the fluid balance, it is now well established that a positive balance is independently associated with an increased mortality rate in septic shock [9, 10]. It makes perfect sense to restrict fluid intake by initiating vasopressors early. In fact, the CENSER-RCT [6] found that the shock was more resolved by 6 hours in the early norepinephrine group (118/155 [76.1%] vs. 75/155 [48.4%]; *P* < 0.001); yet the 28-day mortality did not differ [5]. Despite the large sample size (n = 155 per arm), this trial only included one center and did not evaluate the immediate impact on stroke volume and CO. In the current trial, we try to circumvent these two limitations.

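### ICU stay is compared as a raw duration with no rule for deaths, so an early death ranks as a short stay and the outcome can favour the arm with more deaths

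*Protocol article*

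**What the plan says.** The Outcomes section of the protocol article names eight secondary outcomes, the last four being "vasopressors free days, ICU stay, ventilator free days, and 28 days-Mortality". The section on studied variables lists length of stay among the evolution parameters. The legend of Fig 1 gives the follow-up: "Clinical monitoring will be carried out until discharge in order to determine Vasopressors free days, ICU stay, ventilator free days, and 28 days-Mortality". None of these places says when the stay begins or how a patient who dies in the ICU is counted.

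The analysis is set out under Statistical analyses planned. The population is fixed: "All primary and secondary outcomes analyses are based on the intention-to-treat principle". The method, where normality fails, is also fixed: "we will employ the Wilcoxon-Mann-Whitney test to assess group differences for continuous variables".

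Two rules lie close to the point but do not cover it. The eligibility section says "Patients who die before primary outcome assessment are considered treatment failure", which concerns the 6-hour composite only. The statistical section says that "time to death is calculated from date of sepsis diagnosis to date of death", which sets a time origin for mortality only. The eligibility section also states that "sepsis is only considered for inclusion when it occurred in the ICU to minimize the interventional bias", so a patient may already have spent time in the ICU before randomisation.

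**The concern.** Death ends an ICU stay. If all randomised patients enter the comparison with their observed duration, someone who dies after two days has a better rank than someone who leaves alive after nine. The sentence on imputing missing data does not help, because the stay of a patient who died in the ICU is observed, not missing.

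The error has a direction. A treatment that saves lives tends to lengthen the average stay, and one that causes early deaths tends to shorten it. The Introduction motivates the trial partly by a possible survival benefit, and 28-day mortality is an outcome, so a mortality difference is within what the trial considers possible. ICU stay could then contradict the mortality result for purely arithmetical reasons, or make a harmful arm look efficient.

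A lesser matter is the undefined start. If it is ICU admission, the stay includes days before randomisation that the treatment cannot change.

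**Working it through.** The plan gives no figure for ICU stay, so there is none to reproduce. The group size, 100 per arm, is in the Discussion. Mortality, stay in survivors and time to death are not in the document; all are assumed here.

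**Step 1: direction.** Let a and b be the proportions dying in the ICU in the arm with fewer and with more deaths. Suppose treatment changes nothing else: survivors' stay and time to death are distributed alike in both arms. Let q be the probability that a patient who dies has a shorter stay than one who survives. The Wilcoxon-Mann-Whitney test compares with ½ the probability θ that a patient from the first arm has the longer stay:

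θ = ½[(1−a)(1−b) + ab] + (1−a)b·q + a(1−b)(1−q) = ½ + (b−a)(q−½)

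Whenever deaths tend to be early (q > ½), the arm with fewer deaths is pushed towards the longer stay.

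**Step 2: size.** With n = 100 per arm, the null standard error of the estimate of θ is √[(2n+1)/(12n²)] = √(201/120,000) = 0.0409. Let z = (θ − 0.5)/0.0409. The better arm shows the longer stay with probability Φ(z), and a significantly longer stay with probability of about 1 − Φ(1.96 − z).

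| b − a | q | θ | z | better arm longer | significantly longer |
|---|---|---|---|---|---|
| 10 points | 0.7 | 0.52 | 0.49 | 69% | 7% |
| 10 points | 0.8 | 0.53 | 0.73 | 77% | 11% |
| 10 points | 0.9 | 0.54 | 0.98 | 84% | 16% |
| 20 points | 0.7 | 0.54 | 0.98 | 84% | 16% |
| 20 points | 0.8 | 0.56 | 1.47 | 93% | 31% |
| 20 points | 0.9 | 0.58 | 1.96 | 97% | 50% |

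With no mortality difference the two probabilities are 50% and 2.5%.

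**Step 3: simulation.** Assumptions: survivors' stay from randomisation log-normal with median 9 days and log-SD 0.6; time to death exponential with mean 5 days. These give q = 0.80. At 30% v 40% mortality the better arm has the longer stay in 77% of trials, significantly in 11%; at 20% v 40%, in 93% and 30%. This agrees with the q = 0.8 rows. A second set of assumptions (median 10 days, mean time to death about 4 days) gives median stays of 7.9 v 7.2 days with rejection in 14% of trials at 30% v 40%, and 8.7 v 7.2 days with rejection in 44% at 20% v 40%.

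**Step 4: days before randomisation.** Adding exponential pre-randomisation ICU time with mean 5 days to the first set lowers the 93% to 86% and the 30% to 19%. With equal mortality, rejection stays at about 5%. Such days add noise but do not favour an arm.

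**Step 5: the alternative.** ICU-free days to day 28, with death scored 0, significantly favour the better arm in about 24% of trials at 30% v 40% and 67% at 20% v 40%. If survivors also recover 20% faster at 30% v 40%, plain stay detects the benefit in about 11% of trials and ICU-free days in about 65%. With equal mortality (40% in each arm) and survivors 20% faster, the order reverses: ICU-free days have about 18% power against 26% for stay from randomisation. At log-SD 0.5 the pair is 21% v 33%, and at 0.7 it is 14% v 20%.

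**The case against.** The strongest reply is that the article never says that deaths enter at their raw duration. Intention to treat settles who is analysed and in which arm, not how a death is scored, and a journal article may leave such derivations to an analysis plan that is not shown. The two free-days outcomes are no better defined. This stands in part: silence alone would not be a finding. But the article does fix the variable, the population and the test, and together these give the wrong ranking. ICU stay is also the one item of the three that is not put as free days, so an analysis plan that follows the list faithfully inherits the problem.

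A second reply is that 77% and 93% describe only the sign of a difference, which is 50% by chance, and that with a modest mortality difference a significant wrong-way result is uncommon. That is fair, and both columns are shown above. The Discussion reports that 28-day mortality did not differ in the reference trial; with equal mortality the raw stay is not biased and has more power than the alternative.

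A reader might go further and infer that the plan counts stay from ICU admission, so that someone who falls ill late and recovers fast ranks worst. The documents do not support this. No section gives a start for ICU stay, and the only stated origin, sepsis diagnosis, belongs to mortality. Counted from randomisation, survivors are ordered correctly and only the scoring of deaths remains. Even with admission as the start, the extra days balance in expectation across randomised arms.

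**Conclusion.** The point holds for deaths. As written, ICU stay ranks an early death as a good result and can favour the arm with more deaths. For a 10-point mortality difference and q between 0.7 and 0.9, a significantly longer stay in the better arm is expected in about 7% to 16% of trials; for a 20-point difference, in about 16% to 50%. These figures rest on assumed mortality and stay, on all deaths occurring in the ICU, and on identical survivors' stay in both arms. The direction needs only that deaths come earlier than discharges more often than not.

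On the start of the stay, the supportable statement is narrower: it is not given, and if it were ICU admission the comparison would lose precision without being biased.

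This is one of eight secondary outcomes. The primary outcome has its own rule for death and is unaffected. The matter is worth settling before analysis but does not threaten the main conclusion.

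**What to change.** In the outcome list, replace ICU stay by ICU-free days from randomisation to day 28, with patients who die by day 28 scored 0 (or ranked worst), compared by the Wilcoxon-Mann-Whitney test already named. This fits the vasopressor-free and ventilator-free days in the same list, whose start and death rule can be stated in the same sentence. Report ICU stay from randomisation descriptively, separately for survivors and non-survivors. Record the change as made before the data are analysed by arm.

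The cost is one line in the list and one derivation rule. It needs dates of randomisation, ICU discharge and death, plus a rule for ICU readmission before day 28. The article lists length of stay and mortality as collected but does not name these dates, so the case report form should be checked. The measure mixes survival with stay, so 28-day mortality, already planned, must be shown beside it. If mortality is equal and only survivors' stay shortens, some power is lost (about 18% v 26% on the assumptions above).
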